##### Analysis

We will develop monthly reports to monitor the referral patterns to the THRIVE clinical pathway. The target estimate and effect measure is the time-adjusted difference in participant outcomes [53,54]. The analysis of use outcomes (eg, 30-day readmissions and ED use) will use a mixed effects negative binomial regression model with random effects for the medical team and fixed effects for time to account for the stepped wedge cluster randomized design. Sensitivity analyses may be performed using logistic regression for health service use based on the distribution of the data. We will also examine the stability of effect estimates using generalized estimation equations with small sample adjustment, given the study design [55].

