### Design and Randomization

#### Overview

This is a prospective single-site type 1 hybrid effectiveness-implementation pragmatic stepped wedge cluster RCT. Our stepped wedge design will include a sequential randomized rollout of the intervention to case managers at PAH in 3 steps, and data collection will occur over 18 months. This mixed methods (quantitative and qualitative) study design involves simultaneous collection and analysis of quantitative and qualitative data, giving priority weight to the quantitative data to evaluate program referrals, outcomes, and program fidelity, while qualitative data will evaluate the process through detailed descriptions of perspectives of barriers and facilitators faced by health care providers in implementing the THRIVE intervention [51]. This study includes qualitative interviews and surveys of clinicians and administrators to assess their perspectives on appropriateness, feasibility, and acceptability of THRIVE. Nesting the qualitative interviews within an RCT of the THRIVE intervention will allow us to determine whether the intervention improved primary outcomes (referrals to home care, 30-day readmission, ED use, and connection to primary care providers) and to identify professional and organizational barriers to implementation. Combining these insights with effectiveness outcome data will allow consideration for meaningful contextual factors that are considered critical to the implementation of THRIVE and subsequent outcomes.

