#### Randomization

Groups of case managers (4 in the first group, 4 in the second, and 5 in the third) were randomly assigned by the study methodologist to each sequence using a random number generator. A stepped wedge design—that is, a 1-time crossover design—was used for THRIVE (Table 2).

Specifically, following a baseline data collection period, 4 case managers will be randomized to receive training on the THRIVE clinical pathway. Following training, they begin referring to the THRIVE clinical pathway. At 8-week intervals, the remaining case managers will be trained in the THRIVE intervention and will be able to begin submitting referrals. Since case managers from the sequences work within the same space, the ability to conceal allocation was limited; however, all case managers were made aware of their upcoming ability to refer to the THRIVE clinical pathway.

**Table 2 table2:** Study design for the type 1 hybrid effectiveness-implementation stepped wedge cluster randomized controlled trial of the THRIVE clinical pathway.

Cluster	Baseline (3 months)	Enrollment period 1 (8 weeks)	Enrollment period 2 (8 weeks)	Enrollment period 3 (8 weeks)	Follow-up (18 months)
Sequence 1 (4 case managers)		✓	✓	✓	✓
Sequence 2 (4 case managers)			✓	✓	✓
Sequence 3 (5 case managers)				✓	✓

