##### Outcomes and Measures

The primary outcome includes the referral rate to home care made by CMs compared to baseline and the nonrandomized cluster. The secondary outcomes are 30-day readmissions and ED visits. Additional covariate data at the patient (eg, demographics and comorbidities) and unit levels (eg, type of unit and discharging team or provider) will be collected from analyses. For THRIVE participants, these outcomes will be assessed from the date of hospitalization, which resulted in a referral to THRIVE. For the usual care group, we will identify all readmissions and ED visits occurring after the first index hospitalization identified in the EHR for the calendar year of the study. Outcome measures, guiding framework, data sources, collection, and timing are described in Table 3.

**Table 3 table3:** Summary of outcomes, measures, data sources, collection method, and timing.

Construct and framework					Design		Method of collection			Timing	
**Aim 1: Examine referral patterns, 30-day readmission, and ED^a^ use patterns for participants who receive THRIVE support services compared to those receiving usual care**											
	THRIVE referrals^b^ 30-day readmissions^c^ 30-day ED visits^c^ Primary care visit within 30 days of discharge^c^ Specialty care visit within 30 days of discharge^c^			Stepped wedge cluster randomized controlled trial		Electronic health record			Baseline and at the study end		
**Aim 2: Evaluate the implementation of the THRIVE clinical pathway, including fidelity, feasibility, appropriateness, and acceptability**											

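### The readmission and ED model carries a random effect for the medical team, although case managers are the randomised clusters

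*Protocol article*

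**What the plan says.** Under Design and Randomization, the Overview describes a "sequential randomized rollout of the intervention to case managers at PAH in 3 steps". The Randomization section adds: "Groups of case managers (4 in the first group, 4 in the second, and 5 in the third) were randomly assigned by the study methodologist". Table 2 lists the case managers, by sequence, in the column headed Cluster. After a three-month baseline the steps follow one another: "At 8-week intervals, the remaining case managers will be trained in the THRIVE intervention".

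Under Evaluation, Aim 1, Analysis, the use outcomes (30-day readmission and ED use) get a "mixed effects negative binomial regression model with random effects for the medical team and fixed effects for time". The purpose given for this structure is "to account for the stepped wedge cluster randomized design". The same paragraph adds a possible logistic sensitivity analysis, and a GEE with small-sample adjustment as a check on the stability of the estimates. It names no clustering unit for either.

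The article does not define medical team. The Aim 1 Outcomes and Measures section places team among covariates at "unit levels (eg, type of unit and discharging team or provider" level. Clinician Eligibility and Recruitment lists nurse case managers separately from physicians and advanced practice providers.

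**The concern.** Exposure switches on by case manager. Patients handled by one case manager may share discharge habits, caseload and ward, so their outcomes may be correlated. A model that claims to respect the randomisation has to represent that correlation at the level that was randomised. This one represents a different grouping, which the article does not describe as randomised.

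If case-manager correlation is positive and the team effect does not absorb it, the treatment effect is reported with too small a standard error and p-values fall below .05 too often. Readmission and ED use carry the effectiveness part of Hypothesis 1. They are among the primary outcomes in the Design Overview, though secondary in the Aim 1 Outcomes and Measures section.

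The article names the random effect and states what it is for. It is therefore a stated rule at the wrong level, not detail left to a fuller plan.

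**Working it through.** **The plan's own figure.** The Sample Size section gives 472 (2 × 236) for readmission and 534 (2 × 267) for ED visits, at 80% power and the .05 level. It states no event rates, effect size or ICC, so neither total can be reproduced or refuted. For orientation, halving a 24% rate needs 160 per group and halving a 20% rate needs 199 (two-sided, no continuity correction). The article does not tie its power analysis to those rates. Only the total of about 534 is used below.

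**Inputs from the article.** 13 case managers in sequences of 4, 4 and 5; a three-month baseline, taken as 12 weeks; 8-week steps; about 534 patients; fixed effects for time; a random effect for medical team only.

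**Assumed, because the article gives no value.**
- Case-manager ICC ρ from 0 to 0.10.
- Six medical teams crossed with case managers; or case managers nested in six teams; or two teams nested in each case manager.
- Periods of 12/8/8/8 weeks; or 12/8/8/50 weeks, which total 78 weeks, about the 18 months of data collection.
- A linear mixed model in place of the negative binomial.

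**Step 1: analytic ratio, crossed teams.** Let X hold the period indicators and the treatment indicator, V the true covariance with case-manager ICC ρ, and W the covariance of the team-only model.

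- Model-based variance: A = (X′W⁻¹X)⁻¹
- True variance: A X′W⁻¹ V W⁻¹X A
- R = true variance / model-based variance, for the treatment effect
- Actual error of the nominal 5% test = 2Φ(−1.96/√R)

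| ρ | R, 12/8/8/8 | Error | R, 12/8/8/50 | Error |
|---|---|---|---|---|
| 0 | 1.00 | 5.0% | 1.00 | 5.0% |
| 0.01 | 1.13 | 6.5% | 1.05 | 5.6% |
| 0.02 | 1.26 | 8.1% | 1.10 | 6.2% |
| 0.05 | 1.65 | 12.7% | 1.26 | 8.1% |
| 0.10 | 2.29 | 19.5% | 1.52 | 11.2% |

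Example: at ρ = 0.05 with short periods, 1.96/√1.65 = 1.526, and 2Φ(−1.526) = 0.127.

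**Step 2: simulation.** There were 2,000 null data sets per cell, fitted by REML and tested at |z| > 1.96. The Monte Carlo standard error near 5% is √(0.05 × 0.95/2000) = 0.005. Rejection rates at ρ = 0.01, 0.02, 0.05 and 0.10:

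| Random effect in the model | 12/8/8/8 | 12/8/8/50 |
|---|---|---|
| Team, crossed with case managers | 6.4, 8.4, 12.8, 19.5% | 5.4, 6.3, 7.4, 11.0% |
| Team, case managers nested in it | 6.7, 8.0, 11.2, 18.6% | 5.6, 6.0, 6.7, 8.4% |
| Team, nested within case manager | 5.3, 6.9, 6.0, 7.4% | 5.7, 5.7, 5.7, 5.7% |
| Case manager | 4.5, 5.4, 6.0, 6.1% | 5.2, 5.6, 6.1, 5.3% |

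At ρ = 0 every structure gives 4.0-5.3%. The simulation and the formula agree for crossed teams to within simulation error.

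**The case against.** The strongest reply is that the inflation is conditional. The article gives no ICC, no number of teams and no mapping of teams to case managers. At ρ = 0, or if medical team is loose wording for the case-manager cluster, there is no material inflation. The largest figures need crossed or coarser teams and a data set that stops after the third enrolment period, whereas Table 2 shows a further follow-up column with every sequence exposed. All of this stands, and it limits what can be said about size. It does not remove the mismatch: an analyst who follows the text would fit a term for the wrong unit.

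A second reply is that the GEE with small-sample adjustment covers the problem. It would help only if clustered on case manager, which is not stated, and it is a stability check beside the main model. An article may leave the GEE cluster to the full plan, so that silence is not a fault in itself. Nor does the lack of a small-sample reference in the main model weigh much: with the right random intercept, the uncorrected Wald test already gives about 4-6%.

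Two stronger readings are tempting. A reader might infer that the fault is worst for referral, which is the case manager's own decision. However, the Analysis section assigns this model to the use outcomes only and specifies none for referral. A reader might also infer that 13 units were certainly allocated independently. The Randomization section speaks first of groups being assigned and then of four case managers being randomised, so it can be read either way.

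**Conclusion.** The point holds for the readmission and ED model. The randomised cluster is the case manager, the only random effect is for the medical team, and the sentence claims to account for the cluster randomised design. For a positive case-manager ICC, standard errors are generally too small unless medical team means the case manager or nests within it.

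The size cannot be fixed from the article. Over assumed ICCs of 0.01 to 0.10, the nominal 5% error is about 6-20% (crossed teams, short periods), about 5-11% (crossed teams, long final period) or about 5-7% (teams within case managers). With a case-manager intercept it is about 4-6%. All figures are linear approximations to the negative binomial model. A reader might take a large inflation as established, but only the mismatch and its direction are.

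**What to change.** In the Aim 1 Analysis section, specify a random intercept for case manager as the randomised cluster. Keep medical team, if wanted, as an additional crossed random effect or a covariate. Name case manager as the clustering unit of the GEE check. If medical team was meant as the case manager, say so and use one term throughout.

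A small-sample reference distribution for the main model is a reasonable addition, but secondary. State whether individual case managers or pre-formed groups were allocated to sequences. This must be settled before any permutation test is used, because it determines which reallocations are admissible.

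The cost is a sentence or two in the plan, and intervals that may widen. Each comparison discharge, including those at baseline, must also be linked to its case manager. The article does not say that the EHR extract holds that link, but the design already needs it to assign exposure by sequence. The change is best made before outcomes are analysed, so that it cannot be read as driven by the data.

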##### Equity Evaluation

Our analyses will consider several equity metrics and include interaction terms to capture racial and ethnic differences and biological sex for THRIVE participants compared to patients receiving usual care. Using all payor data obtained from the EHR, we will also conduct a secondary analysis to examine health service use across all insurance payor types for THRIVE participants and the usual care group, allowing a proxy measurement for differences across socioeconomic strata.

#### Aim 2

Aim 2 is to evaluate the implementation of the THRIVE clinical pathway, including fidelity, feasibility, appropriateness, and acceptability.

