This study will deploy a type 1 hybrid effectiveness-implementation stepped wedge cluster RCT across a single hospital in Philadelphia [43]. The advantage of this trial design is that it offers an efficient and practical way to introduce THRIVE to new sites while reducing the ethical concerns of withholding an intervention that has shown benefit for economically disadvantaged populations. This study will also be guided by the Exploration, Preparation, Implementation, Sustainment framework; Proctor’s outcomes framework; and the Health Equity Implementation Framework (HEIF) [44-46]. The HEIF adapts the Integrated Promoting Action on Research in Implementation in Health Services framework. The HEIF proposes determinants that are believed to predict the successful and equitable implementation of an intervention. The 3 health equity domains included in the HEIF include cultural factors, clinical encounter factors, and societal context [47]. Our use of the framework will help us to detect any factors that might lead to uneven referrals to THRIVE; disparate benefits to the intervention; and any barriers that might prevent organizations, health care providers, or administrators from engaging in the intervention. In their recently published paper, Brownson et al [48] noted that “Incorporating a strong equity focus in implementation science requires not only a deliberate emphasis on the needs, culture, and history of the populations and communities but also more critical analyses and deeper understanding of systems and policies, including care delivery and provider attitudes from which inequities might arise.” They propose action steps for making health equity more prominent in implementation science. To that end, we incorporate and adapt our study design to ensure principles of equity in the approach to data collection, measures, contextual alignment, and dissemination practices (Table 1).

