	**Proctor implementation outcomes**										
		Acceptability^i^ Appropriateness^j^ Feasibility^k^	Mixed methods approach to determine the Proctor implementation outcomes					Survey and interviews with clinicians and administrators			8-week postintervention from the start of each sequence and at the study end
		Fidelity^l^	Retrospective chart review					Standardized THRIVE checklist			Monthly

^a^ED: emergency department.

^b^Proportion of THRIVE referrals of those who are THRIVE eligible.

^c^Proportion of THRIVE participants experiencing the outcome within 30 days of discharge compared to usual care group.

^d^Organizational commitment to addressing disparities.

^e^Relative advantage of THRIVE to patients, degree of fit with existing practice, competing demands, and bias.

^f^Structures outside of the hospital that affect patient care.

^g^Organizational values, culture embedding, and championing adaption.

^h^Organizational priorities and goals and readiness for change and culture or climate.

^i^How fair or reasonable THRIVE is deemed.

^j^To what extent THRIVE seems suitable.

^k^The practicality and ease of delivering THRIVE.

^l^Fidelity to THRIVE’s core components.

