### Conclusions

The goal of THRIVE is to reduce disparities and improve postdischarge care transitions for Medicaid-insured patients through a feasible system-level intervention that is satisfying for THRIVE participants, clinicians, and their teams in hospitals and home care settings. By using our equity-focused case management services and leveraging the power of the electronic medical record, THRIVE creates efficiencies by identifying high-need patients, improving communication across acute and community-based sectors, and driving evidence-based care coordination. This study will advance the field of equity-focused evidence-based interventions by testing both the effectiveness of patients’ health improvement and the adoption of THRIVE by typical clinical practices. It will add important findings about how the infusion of equity-focused principles in the design and evaluation contributes to both implementation and effectiveness outcomes.

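### The effect measure is stated as a difference, but the equity evaluation rests on interaction terms whose scale is not stated and would by default be a ratio

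*Protocol article*

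**What the plan says.** All references are to the protocol article.

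- **Effect measure** (Evaluation, Aim 1, Analysis): "The target estimate and effect measure is the time-adjusted difference in participant outcomes". No unit is given. Footnote c of Table 3 defines the 30-day outcomes as a "Proportion of THRIVE participants experiencing the outcome within 30 days of discharge compared to usual care group", so a difference in proportions is the natural reading.
- **Model** (same section): the analysis of use outcomes "will use a mixed effects negative binomial regression model with random effects for the medical team and fixed effects for time". No link function is stated. "Sensitivity analyses may be performed using logistic regression for health service use based on the distribution of the data". Generalized estimating equations with a small-sample adjustment are mentioned as a stability check, also without a link.
- **Equity analysis** (Equity Evaluation): besides a number of equity metrics, which are not named, the analyses are to "include interaction terms to capture racial and ethnic differences and biological sex for THRIVE participants compared to patients receiving usual care". A separate secondary analysis compares service use across payor types.
- **Purpose** (Conclusions): "The goal of THRIVE is to reduce disparities and improve postdischarge care transitions for Medicaid-insured patients".

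**The concern.** Whether a treatment effect differs between groups depends on the scale whenever the groups start from different risks. The article declares a difference as its effect measure. The one concrete tool it gives for racial, ethnic and sex differences would, with the named models under their usual links, be estimated as a ratio of ratios.

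A reader of the results could then take a null interaction to mean that a between-group gap was left unchanged, when in percentage points it had shrunk. Equally, an interaction above 1 could be taken to mean that the higher-risk group was left further behind, when the gap had narrowed. For a trial framed around disparities, the scale should be settled before the data are seen.

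**Working it through.** The article gives no figure for this analysis that could be reproduced. The check is whether the two scales can disagree, and by how much.

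**Inputs (assumed).** The article gives no readmission risks by race, ethnicity or sex. Take usual-care 30-day risks of 24% in group A and 16% in group B. The 24% matches the readmission figure for Medicaid adults aged 45-64 in the Background, but that is not a rate for any race or sex group. The 16% and all rate ratios are assumptions.

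**Formulas.** With usual-care risks a0 and b0, and rate ratios RR_A and RR_B:
- ratio interaction = RR_A / RR_B
- gap under usual care = a0 − b0
- gap under THRIVE = a0·RR_A − b0·RR_B
- the gap narrows if and only if a0(1 − RR_A) > b0(1 − RR_B)

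**Case 1, opposite directions.** RR_A = 0.75, RR_B = 0.70.
- A: 24% × 0.75 = 18.0%, a fall of 6.0 points. B: 16% × 0.70 = 11.2%, a fall of 4.8 points.
- Interaction: 0.75/0.70 = 1.07, read as less benefit in A.
- Gap: 8.0 → 18.0 − 11.2 = 6.8 points, so it narrows.
- Odds scale: odds ratios (0.18/0.82)/(0.24/0.76) = 0.695 and (0.112/0.888)/(0.16/0.84) = 0.662; their ratio is 1.05. The logistic model points the same way as the rate ratio.

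**Case 2, null interaction.** RR = 0.70 in both groups.
- A: 16.8%, a fall of 7.2 points. B: 11.2%, a fall of 4.8 points.
- Interaction: 1.00. Gap: 8.0 → 5.6 points.

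**Case 3, equal absolute benefit.** A fall of 5 points in both.
- A: 19%, RR 0.79. B: 11%, RR 0.69. Interaction: 0.792/0.688 = 1.15.
- Gap: 8.0 → 8.0 points.

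**Range of disagreement.** With these risks and RR_B = 0.70, the gap narrows as long as RR_A < 1 − (16 × 0.30)/24 = 0.80. The two scales therefore point in opposite directions for RR_A between 0.70 and 0.80, that is, for interactions between 1.00 and 0.80/0.70 = 1.14. With assumed risks of 30% and 20% and RR_B = 0.50, they do so for RR_A between 0.50 and 0.667 (interactions up to 1.33).

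**Precision.** Assume 534 patients (Sample Size section) split evenly over two groups and two conditions, 133.5 per cell, with no clustering. In Case 1:
- SE of the log interaction = √[Σ(1 − p)/(np)] = √(20.90/133.5) = 0.396. The 95% interval for 1.07 is about 0.49 to 2.33.
- Difference between the risk differences = −6.0 − (−4.8) = −1.2 points. SE = √[Σp(1 − p)/n] = √(0.5639/133.5) = 0.065, so −1.2 ± 12.7 points.

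Neither scale would be informative at this size. Unequal groups or clustering would usually widen both intervals.

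**The case against.** The strongest reply is that the article does not say what a reader might infer from it. It states no link function, does not tie the interaction terms to the negative binomial model, and lists them beside unnamed equity metrics that could include an absolute one. The difference it declares could be obtained from the same model by standardised prediction, a step usually left to the analysis plan, which is not shown. All of this stands. It rules out saying that the plan commits to a ratio-scale test or has a rule for declaring a disparity narrowed or not; it has neither. What remains is that one section names a difference, the next names interaction terms, and nothing joins the two.

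A reader might also treat "disparate benefits to the intervention", in the Introduction, as the purpose of these interaction terms. The documents do not support that: the phrase describes what the Health Equity Implementation Framework should help detect, and Table 3 assigns that to a mixed methods approach under Aim 2 based on interviews. The stated goal of reducing disparities is likewise framed around people insured by Medicaid, and the payor-type analysis addresses that separately.

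Finally, at about 534 patients neither scale could support a firm conclusion. This also stands. It limits the weight of the point and is why the added estimates should be labelled exploratory. It does not remove the need to say which quantity is being estimated.

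**Conclusion.** The point holds as an unresolved scale, not as a wrong analysis. The stated effect measure is a difference; the equity evaluation relies on interaction terms that, under the standard links of the named models, are ratios. If usual-care risks differ between groups, a null or mildly adverse ratio interaction can accompany a narrowing gap: 1.07 with 8.0 → 6.8 points, or 1.00 with 8.0 → 5.6 points, in the illustrations.

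This rests on three assumptions: a log or logit link, interactions fitted in the models that the Analysis section names, and unequal usual-care risks. The group risks and rate ratios are invented for illustration. It would go too far to say that the trial's conclusion on disparities will be reversed, or that the absolute scale must be the only equity measure; that choice is a preference. Importance: a cheap improvement.

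**What to change.** In the Equity Evaluation, or in the analysis plan if it does not already do so:

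1. State the model that carries the interaction terms and the scale on which they are read.
2. From that same fitted model, compute standardised 30-day risks under THRIVE and under usual care in each race/ethnicity and sex group.
3. Beside the ratio interaction, report the risk difference within each group and the difference between those risk differences with a confidence interval. The latter is the change in the between-group gap.
4. Label these results exploratory.

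The cost is a short addition to the text and a little post-estimation code, with no new data or patients. The drawback is wide intervals, especially in small groups.
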